## 13 Data Management

We will use the REDCap (Research Electronic Data Capture) system for data management, which provides secure, web-based applications that are flexible enough to be used for a variety of types of research, provide an intuitive interface for users to enter data and have real time validation rules (with automated data type and range checks) at the time of entry. These systems offer easy data manipulation with audit trails for reporting, monitoring and querying patient records, and an automated export mechanism to common statistical packages (SPSS, SAS, Stata, R/S-Plus). REDCap

[figure not shown]

A pilot study examining the microbiotal composition in children with autism after use of *Bifidobacterium infantis* and milk oligosaccharides.

servers are housed in a local data center at UC Davis Health System and all web-based information transmission is encrypted. REDCap was developed specifically around HIPAA-Security guidelines. REDCap has been disseminated for use locally at other institutions and currently supports 240+ academic/non-profit consortium partners on six continents and over 26,000 research end-users ([www.project-redcap.org](http://www.project-redcap.org)).

The subjects' health information, along with the identifiers, will be kept with the investigator until the conclusion of the study, or when immediate access is no longer required. Thereafter, the information may be transferred to a records and information management company for long-term storage, or to a UCDMC long term storage facility. When the investigator no longer require the information (but no sooner) than 5 years, the documents will be securely shredded. All study personnel will have access to study records, data, and specimens. Every attempt will be made to ensure that the personal and medical information of the subject will be kept private.

#### **14 Provisions to Monitor the Data to Ensure the Safety of Subjects**

This study is low risk. The products used in this study are dietary supplements designed to balance the intestinal flora and are not intended to "diagnose, cure, mitigate, treat or prevent disease." Any evidence of illness or infection will be thoroughly evaluated.

[name], a board-certified developmental-behavioral pediatrician, will monitor all reported adverse events and [name] and [name], two pediatricians not involved in the study, will be available to informally review adverse events.

Adverse events will be queried as part of the medical history at baseline and weeks 5, 7, and 12, as well as through phone calls on weeks 2/3 and 9/10. Any adverse events that could be related to the study will be reported to the IRB as required by IRB guidelines.

#### **15 Withdrawal of Subjects**

The study team reserves the right to withdraw subjects from the study for reasons including, but not limited to, adverse events and non-compliance. The caregivers of a subject may also withdraw their son or daughter from the study.

If a subject is withdrawn from the study early, caregivers will be asked to return to the MIND Institute for a termination visit which will include a visit with a study physician who can assess for adverse events and general safety of the subject.

Information gathered about a subject who has terminated the study early, as well as any blood and stool samples, will be kept for analysis unless the subject's caregivers specifically ask for this information to be removed for analysis. Caregivers will be informed of this in the event of an early termination.

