## 4 Objectives

**AIM 1. To characterize stool microbiotal composition and immune markers after administration of a probiotic with and without a prebiotic in children with autism.**

Hypothesis 1.1: Synbiotic administration of *Bifidobacterium infantis* (probiotic) and bovine milk oligosaccharides (prebiotic) will alter the composition of stool microbiota, with greater increases in commensal actinobacteria (including *B. infantis*) and decreases in pathogenic proteobacteria than *B. infantis* alone.

Hypothesis 1.2: Synbiotic administration of *Bifidobacterium infantis* and bovine milk oligosaccharides will alter serum immune (cytokine, immunoglobulin) measures.

**AIM 2 (exploratory). To determine tolerability of *Bifidobacterium infantis* and bovine milk oligosaccharides in children with autism.**

Hypothesis 2.1: *Bifidobacterium infantis* and bovine milk oligosaccharides will be well tolerated in children with autism, as measured by gastrointestinal and behavioral symptoms.

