## **7 Study-Wide Number of Subjects**

We intend to enroll twenty subjects in hopes of having ten subjects complete the protocol.

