## 10 Study Endpoints

The primary endpoint will be change in intestinal microbiotal composition. Secondary endpoints will include change in serum immune markers, fecal and plasma zonulin, fecal elastase-1, fecal and urinary protein/peptide profiles, and fecal and urinary microbial putrefaction metabolites.

Tolerability will be monitored through GI questionnaires, behavioral questionnaires, and clinician assessment.

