**Table 1. Study visits, assessments, and procedures.**

|                            | Week 0                                    | Week 2/3 | Week 5  | Week 7  | Week 9/10 | Week 12 |
|----------------------------|-------------------------------------------|----------|---------|---------|-----------|---------|
| Assessment                 | Baseline Visit                            | Call 2   | Visit 3 | Visit 4 | Call 2    | Visit 4 |
| ADOS/ADI-R                 | Obtained Previously From A Reliable Rater |          |         |         |           |         |
| IQ / Developmental Testing | Obtained Previously From A Reliable Rater |          |         |         |           |         |
| ABAS-II                    | X                                         |          |         |         |           |         |
| Physical Exam/ Vitals      | X                                         |          | X       | X       |           | X       |
| Adverse Events             | X                                         | X        | X       | X       | X         | X       |
| GI Questionnaires          | X                                         |          | X       | X       |           | X       |
| ABC                        | X                                         |          | X       | X       |           | X       |
| RBS-R                      | X                                         |          | X       | X       |           | X       |
| Stool Sample               | X                                         |          | X       | X       |           | X       |
| Urine Sample               | X                                         |          | X       | X       |           | X       |
| Blood Draw                 | X                                         |          | X       | X       |           | X       |

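### The GI and behaviour questionnaires that measure tolerability are not scheduled at the early-termination visit, so children who stop mid-period have no on-product score

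*Protocol*

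**What the plan says.** Hypothesis 2.1 (Section 4, the exploratory Aim 2) states that the products "will be well tolerated in children with autism, as measured by gastrointestinal and behavioral symptoms". Section 10 names the tools: "Tolerability will be monitored through GI questionnaires, behavioral questionnaires, and clinician assessment". That makes three, two of them questionnaires.

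The protocol's Table 1 ("Study visits, assessments, and procedures") schedules the GI questionnaires, the ABC and the RBS-R at weeks 0, 5, 7 and 12. The phone calls at weeks 2/3 and 9/10 cover adverse events only. There is no early-termination column.

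Under Section 15 the study team may withdraw a child "for reasons including, but not limited to, adverse events and non-compliance", and caregivers may also withdraw the child. The family is then asked to come back, which the protocol describes as "a termination visit which will include a visit with a study physician who can assess for adverse events and general safety of the subject". Under the same section, data already gathered "will be kept for analysis unless the subject's caregivers specifically ask for this information to be removed for analysis".

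On numbers, Section 7 says: "We intend to enroll twenty subjects in hopes of having ten subjects complete the protocol". Section 26 explains that the surplus covers screening failures and early terminations together.

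**The concern.** Two of the three tolerability tools are not planned at the moment when a tolerability problem may be at its clearest, namely when a child stops because of symptoms. This is a matter of data collection, which the protocol fixes. The rule in Section 15 for keeping data preserves what was gathered, but neither that rule nor an analysis plan can supply a score that was never taken.

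The scores matter because of who is enrolled. Every child enters with diarrhoea, constipation or both (Section 6), so GI intolerance is likely to show as a change from an already abnormal baseline. A repeated scored instrument is made to measure such a change. An adverse-event enquiry gives no score to compare with baseline. On the behavioural side the gap is wider: the ABC and RBS-R are the only repeated behavioural instruments in Table 1, and neither is scheduled between visits.

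At stake is the questionnaire evidence for Hypothesis 2.1. If children who stop tend to be those with worse symptoms, the on-product scores come disproportionately from children who did well.

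**Working it through.** No stated figure in the protocol depends on this point, so there is none to reproduce. The check sets Section 11 (dosing periods), Table 1 and Section 15 side by side.

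**Step 1. Which scores are on-product.** Section 11 gives 5 weeks on one product, 2 weeks of washout, then 5 weeks on the other: 5 + 2 + 5 = 12 weeks. Week 5 ends the first period, week 7 ends the washout and week 12 ends the second period. Of the four questionnaire times, only weeks 5 and 12 reflect time on a product, one score per product.

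**Step 2. What a child has at each stopping time,** following the schedule as written:

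| Child stops | Scheduled scores held | On-product score, first product | On-product score, second product |
|---|---|---|---|
| Before week 5 | week 0 | none | not started |
| During washout, after week 5 | weeks 0, 5 | week 5 | not started |
| Between weeks 7 and 12 | weeks 0, 5, 7 | week 5 | none |
| Completes | weeks 0, 5, 7, 12 | week 5 | week 12 |

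Stopping within either dosing period leaves no on-product questionnaire for the product being taken. Stopping during washout loses no score for a product already taken.

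**Step 3. How many children.** Up to 20 are enrolled for a hoped-for 10 completers, so the surplus is 20 − 10 = 10. It includes screening failures and no split is given. If ten complete, early terminations lie between 0 and 10.

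**Step 4. Direction, by illustration.** The rates below are assumptions and do not come from the protocol. Suppose 10% of the 10 completers are intolerant, and 2 to 10 further children stop early, of whom 30% to 80% are intolerant. The proportion among all treated is (10 × 0.10 + m × p) / (10 + m), where m is the number who stop and p the proportion of them who are intolerant:

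- m = 2, p = 0.30: (1 + 0.6) / 12 = 13%
- m = 5, p = 0.50: (1 + 2.5) / 15 = 23%
- m = 10, p = 0.80: (1 + 8) / 20 = 45%

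A summary resting on completers alone would show 10% in each case. With m = 0, or with p equal to the completers' 10%, the two agree and nothing is lost but precision. The illustration shows which way the error runs if stopping is related to intolerance. It does not estimate the size.

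**The case against.** The strongest reply is that the gap is narrow and that several stronger readings fail. Most of that reply stands.

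- **A reader might infer that the termination visit consists only of a safety check.** The wording says what the visit includes and excludes nothing. The fair statement is that the questionnaires are not specified there.
- **A reader might infer that early stoppers vanish from Aim 2.** They do not. Clinician assessment is one of the three tools in Section 10, and the termination visit can supply it. Adverse events are queried at visits and by phone (Section 14), and they can capture the GI effects listed in Section 16. Parents keep a Bristol stool log throughout participation (Section 11). Data already gathered are kept.
- **A reader might infer that the product at withdrawal would be hidden.** The pharmacy randomises the sequence, the periods are fixed, and unblinding follows the last participant's completion (Sections 11 and 21). Sequence plus stopping date gives the product.
- **A reader might infer that Aim 2 is restricted to completers, or that half are forecast to drop out.** Nothing restricts Aim 2 in this way, and Section 15 points towards using all retained data. Twenty is a recruitment ceiling that also covers screening failures.
- **Aim 2 is exploratory.** The primary endpoint is microbiota, and no sample-size figure depends on this point.

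What the reply does not remove is the missing scores. The stool log records bowel movements and consistency; it does not record pain, vomiting, irritability or repetitive behaviour. Adverse-event reports and a physician's assessment are useful, but they cannot be compared with the baseline GI, ABC and RBS-R scores.

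**Conclusion.** The point holds in limited form. The protocol does not schedule the GI questionnaires, ABC and RBS-R at early termination, so a child who stops within a dosing period has no planned on-treatment questionnaire score for that product. Because adverse events are a named reason for withdrawal, the loss may be informative, and the questionnaire part of Hypothesis 2.1 can then lean towards a finding of good tolerability.

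The size cannot be determined from the protocol: between 0 and 10 children could be affected, and their reasons for stopping are unknown. The conclusion assumes that sites follow Table 1 and Section 15 as written and that some withdrawals reflect poor tolerance. If questionnaires were in practice given at the termination visit, the gap would close. The change is a worthwhile, inexpensive improvement to an exploratory aim. The primary microbiota objective does not turn on it.

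**What to change.** - **Table 1:** add an early-termination column marking the GI questionnaires, ABC and RBS-R, alongside the adverse-event and physician assessment already planned.
- **Section 15:** add a sentence that at the termination visit, or by phone or post if the family cannot attend, these forms are completed, the stool log is retrieved, and the last-dose date and study period are recorded. The last-dose date is needed to judge whether a score reflects time on product.
- **Reporting:** state that tolerability is reported for all children dosed, with each early-termination score attributed to the product taken at withdrawal. Period and date can be recorded blind and linked to the sequence after unblinding, so no early unblinding is needed.

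The cost is protocol wording. The forms are already in use and the visit is already planned. The downside is a somewhat longer visit, or an extra call or mailing, for families who are leaving, and some may decline.

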#### **16 Risks to Subjects**

The most common anticipated risks due to participation in the study include anxiety, frustration, fatigue, or embarrassment during the answering of questionnaires, study assessments

[figure not shown]

A pilot study examining the microbiotal composition in children with autism after use of *Bifidobacterium infantis* and milk oligosaccharides.

and testing, as well as during the medical history and exam. Breaks will be offered to subjects as needed.

Bifidobacteria are abundant in the large intestines soon after birth (Borriello, Hammes et al. 2003). Probiotics are considered to have little or no pathologic potential (Mäkeläinen, Tahvonen et al. 2003) and have been used safely in children with few side effects (Zoppi, Cinquetti et al. 2001)(Gopal, Prasad et al. 2003) at doses similar to those in the proposed study. Previous studies have also documented the tolerability and safety of BMO (Buddington, Williams et al. 1996, Kleessen, Sykura et al. 1997, Pedersen, Sandström et al. 1997, Bouhnik, Vahedi et al. 1999, Kruse, Kleessen et al. 1999, Bouhnik, Raskine et al. 2004, Puccio, Cajozzo et al. 2007, Ziegler, Vanderhoof et al. 2007, Chouraqui, Grathwohl et al. 2008, Silk, Davis et al. 2008). The potential side effects associated with synbiotics may include: vomiting, belching, bloating, flatulence, diarrhea, rumbling stomach, and stomach cramps. Infection is an extremely rare and unlikely side effect (Gasser 1994, Saxelin, Chuang et al. 1996), with estimates that they may represent up to 0.05%–0.4% of cases of infective endocarditis and bacteremia (Borriello, Hammes et al. 2003). Existing data suggest that the risk of bacteremia is <1 case per million individuals (Borriello, Hammes et al. 2003). Any immunocompromised individuals will be deemed ineligible, although probiotics have been considered safe to use even in individuals with HIV (Wolf, Wheeler et al. 1998, Cunningham-Rundles, Ahrné et al. 2000). Phone calls will be conducted throughout the study to assess adverse events. [name] contact information will be provided to all subjects' caregivers for emergencies related to the study.

A potential risk is the chance of infection or bleeding at the site where the venous blood draw is completed. This site will be carefully cleaned prior to the draw and an appropriate dressing will be applied to the area.

Every attempt will be made to ensure that the personal and medical information of the subject will be kept private; however, we cannot guarantee total privacy. The subject's personal and medical information may be given out if required by law. All the data obtained from this study will be kept confidential. Only research personnel on the IRB approved protocol will have access to the data. Electronic data will be password protected and physical data will be stored in a locked file room.

Because this study involves young children between the ages of 2 and 11 years old, all personnel associated with the study will pay special attention to all potential risks associated with the study.

Psychological, social, or legal injury is not anticipated.

## 17 Potential Benefits to Subjects

This study aims to characterize the microbiotal composition of stool in children with autism or ASD after synbiotic administration without the specific goal of clinical improvement. As such, each subject may not personally receive any direct benefit from participation in this study. Participants have been provided with this information in the consent form.

[figure not shown]

A pilot study examining the microbiotal composition in children with autism after use of *Bifidobacterium infantis* and milk oligosaccharides.

Despite not offering direct benefits to patients, participants will undergo neuropsychological assessments, the results of which may be made available to the family of participants on request. Participants will also benefit from the medical exams offered through the study. Additionally, a complete blood count will be conducted as a part of this study. Participants will be informed of clinically significant findings from either the medical exam or CBC as appropriate.

## 18 **Vulnerable Populations**

This study intends to enroll developmentally disabled children with autism or ASD who will be too young to consent to participate to this study. As such, reliable and competent caregiver(s) (such as (a) parent(s) or other legal guardian) must give consent to participate in this study. The caregivers of the participant will be informed of all known risks and potential benefits associated with the study.

Because this study involves young children between the ages of two and eleven years old with developmental disorders all study staff will pay special attention to the potential risks associated with the study. We have done research with developmentally disabled and cognitively impaired individuals of all ages for many years. Consent for individuals with cognitive disability is always signed by parent or caregiver, and no study-specific procedures will be done for any subject prior to consent.

A letter of information will be supplied and explained to all participants who are between the ages of 8 and 11 years old (inclusive). As this study is not open to subjects aged 12 and older, the study does not have an Assent Form available.

## 19 **Multi-Site Research**

This is a single site research study.

## 20 **Community-Based Participatory Research**

Not applicable.

## 21 **Sharing of Results with Subjects**

The data gathered regarding microbiotal composition will be for research purposes and will be of limited use to the families. Thus, data collected throughout this study will not be made available with the exception of developmental/cognitive and/or adaptive scores if requested. These scores will be released to the families in the form of a research report.

Study participants will be unblinded as to which treatment was received during each arm of the trial when the last participant has completed the trial. Unblinding will be conducted by a study physician.

[figure not shown]

A pilot study examining the microbiotal composition in children with autism after use of *Bifidobacterium infantis* and milk oligosaccharides.

## 22 Setting

### The UC Davis MIND Institute

We will recruit and patients from existing MIND Institute research studies and the Volunteer Research Registry. Participants will be evaluated at the MIND Institute Research Clinic. The MIND Institute is a multi-purpose research facility focusing on patients with autism spectrum disorders and other neurodevelopmental disorders. The MIND Institute is well equipped with multiple patient exam rooms available for questionnaires, surveys, and physical exams. This will be the main study site, as recruitment, screening, and patient visits will occur at the MIND Institute. The use of space at this facility has been pre-approved by the MIND MICRO committee.

In order to ensure that multiple visits to the MIND Institute is not a barrier for participating in the study, home visits for some assessments will be offered to families who would otherwise not be able to participate in the study.

### [name] Lab

[name] has a well-equipped anaerobic microbiology lab and has previously evaluated a wide variety of bifidobacteria species including the ability of specific micro-organisms to grow in oligosaccharide medium. [name] lab also has thermocycler equipment to quantify bifidobacteria. The [name] laboratory is in the new Robert Mondavi Institute for Wine and Food Science at UC Davis. This includes a ~1000 square-foot lab equipped for all proposed microbiological and biochemical work. The laboratory is equipped with a specially designed Coy anaerobic chamber with incubator, a BioTek PowerWave 340 plate reader and all the necessary tools to perform the prebiotic screening and microbial BMO-functionality assays. Existing equipment that will be used in this project are: incubators, 2 anaerobic hoods, shakers, biosafety hood, ovens, UV-Vis spectrophotometers, electrophoresis apparatus, gel documentation equipment, refrigerators, freezers, cell disrupters, microscopes, table top centrifuge, microcentrifuges, high-speed centrifuge, several -80C freezers, 2 real time thermocyclers, and 2 microtiter plate readers for bacterial growth studies. The laboratory is equipped with five Macintosh computers, two Pentium PC computers, and several common printers.

